# Addendum to Analysis Plan

## **VDAART Analysis Plan (Addendum to Protocol)**

All analyses of primary and secondary outcomes stated in the VDAART Protocol will be performed using the intent-to-treat (ITT) paradigm, unless specifically stated.

### **I. Definition of outcomes.**

**A. Asthma and recurrent wheezing.** The primary outcome of the trial will be development of a doctor's diagnosis of asthma and/or recurrent wheeze. While asthma is acknowledged to have its roots in early life, making a definite diagnosis is difficult until the child is older, and wheezing illnesses may be precursors of an asthma diagnosis. Thus, we will have a composite definition for the primary outcome.

- Asthma will be defined as a parent's report of physician's diagnosis at any time during the first three years of life, based on questionnaire responses. For time-to-event analyses, the time of incident asthma will be determined by the time of first positive questionnaire response.
- Recurrent wheezing will be defined as at least one report of wheezing in the third year of life plus any report of wheezing in any of the first two years of life.

Recognizing that wheezing symptoms may be modified by medication use, variable age of onset, and other variables, the following will be included in the composite outcome:

- children who had at least one wheezing episode (during the 1st 2 years of life), plus an asthma controller medication (defined as steroid inhalers or nebulizers OR steroid pills or liquids OR leukotriene modifiers) in the third year
- children who did not report any wheezing in the first 2 years but who report 2 separate episodes of wheezing in the third year OR are on controller medication (defined as above) on at least 2 separate reports in the third year OR at least 1 report of wheezing and at least 1 separate report of controller medication use in the third year

For recurrent wheezing (and the other wheezing phenotypes), the time of incident recurrent wheezing will be determined by the time of first report of wheezing, for time-to-event analyses. In the event that the child meets the definition based solely on the use of controller medication, the first report of use of this controller medication will be used to determine the time of onset of wheezing for time-to-event analyses.

For these outcomes, because the questions were asked every 3 months, and recognizing that missing questionnaires occurred, event times will be treated as interval-censored.

**B. Eczema.** Eczema will be defined as a positive response to parent's report of physician's diagnosis at any time during the first three years of life based on the questionnaire responses.

**C. Lower respiratory tract infections (LRI).** Lower respiratory tract infections (LRIs) will be defined based on parental responses to questionnaires. LRIs will be defined as a parental report of a physician's diagnosis of pneumonia, bronchiolitis, bronchitis, or croup (laryngotracheobronchitis).

LRIs may occur multiple times over a three-year period in a child. Information on repeated episodes of LRI will be employed for rate estimation and comparison.

**D. Total and specific IgE.** Total and specific serum IgE will be measured from cord blood samples, and from year 3 samples from the children. Total IgE will be analyzed as a continuous outcome. Sensitization will be defined as any specific IgE  $\geq 0.35$  IU.

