### P.3 Multiple comparisons.

All pre-specified hypotheses will be tested individually at the 0.05 level of significance, using a conservative two-sided alternative hypothesis (even when the stated hypothesis is one-sided). More specifically, the primary and secondary hypotheses of Vitamin D supplementation and Asthma/Recurrent Wheeze, Allergy/Eczema/LRI, will not be adjusted for multiple comparisons, since they have been defined a priori and are limited in scope. Additionally, an interim analysis plan has been developed for the primary outcome to adjust for the number of times (3) asthma and/or recurrent wheeze will be analyzed over the study period. Since 25(OH)D status is being examined in 5 separate analyses (maternal plasma at 26-28 weeks, maternal plasma at delivery, cord blood at delivery, infant plasma at years 1 and 3), this analysis will be adjusted for 5 multiple comparisons (i.e., using Bonferroni correction). Finally, any findings with respect to interaction terms (i.e., exploring whether environmental and demographic covariates affect the relationship between Vitamin D supplementation and the outcome of interest) for any of the hypotheses will be adjusted (i.e., using FDR methodology) for the number of models tested, and interaction testing will be limited to those defined in sections D.14.2a-c, in order to limit the potential for spurious findings. Any serendipitous findings coming from exploratory analyses will be clearly reported as such, and test statistic p-values will be adjusted by the number of exploratory hypotheses considered (using FDR or another appropriate procedure for multiple comparisons adjustment).

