## K. Interim Analyses

For each specific aim, we have developed an interim analysis plan to monitor the endpoints over the course of the study. For specific aims 1 and 3, which monitor primary (asthma and recurrent wheeze) and secondary (e.g., eczema, LRI) outcomes in the infants, this sequential monitoring plan consists of three interim analyses (conducted at year 3 month 5, year 4 month 5, and year 5 month 5 and a final analysis at the end of the study, when the three-year follow-up has been completed on all subjects. For specific aims 2 and 4, which involve outcomes monitored at delivery (i.e., circulating 25(OH)D levels in maternal and cord blood), there will be two interim looks and a final analysis (year 2 month 5, year 3 month 5, and year 4 month 5, respectively).

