For maximum flexibility in the analysis, we will use a Lan-Demets alpha spending function with O'Brien-Fleming bounds. The software program LANDEM (<http://www.biostat.wisc.edu/landemets/>) was used to calculate the crossing boundaries, which, for the first and third specific aims are  $|z|=4.3329$ ,  $2.9631$ ,  $2.3590$ , and  $2.0141$ , at the first, second, third and final analyses, respectively. For the second and fourth specific aim, with 3 looks in total, the crossing boundaries are  $|z|=3.7103$ ,  $2.5114$ , and  $1.993$  at the first, second looks and final analysis, respectively. While the looks in the interim analyses have been predetermined, the Lan-DeMets procedure provides a spending function approach which does not require pre-specification of the frequency or timing of interim looks. This can be advantageous if the timing of data collection varies or if the need for more frequent monitoring arises. Conservative O'Brien-Fleming bounds are used to preserve most of the type-I error for the final analysis. For all specific aims, the hypothesis tests are conducted with two-sided alternatives (i.e. a two-sided p-value). If the boundaries are crossed for efficacy endpoints at any interim analyses, for any of the aims, the study will continue. If the boundaries are crossed in Specific Aims 2-4, the primary specific aim, whether Vitamin D supplementation in pregnancy is associated with a reduction in asthma and/or recurrent wheeze risk, still needs to be assessed, thus the study should continue to monitor this endpoint. If the boundaries are crossed during an interim analysis of the primary aim, the study will also be continued, as the target intervention period (i.e., pregnancy) will have passed for all recruited subjects, and will feel that it is most important to examine the impact of this intervention on the children at 3 years of age. If the study is stopped early due to the success of the intervention, important clinical and outcome information may be lost. Therefore, we feel that it is important to continue the study even if interim analysis boundaries are crossed. The only situation when consideration will be given to prematurely stopping the trial will be for safety considerations. It is inevitable that adverse health events will be observed in all contexts noted above even if both treatments have no biological effects whatsoever. If the rate of adverse events on the active arm substantially and persistently exceeds the rate on the control arm, even in the absence of biological theory that connects the adverse events to vitamin D exposures, and no evidence of therapeutic effect or benefit of the active treatment is apparent in interim analyses, then premature termination of the study may be considered on safety grounds. The DSMB will be asked to articulate

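### Dating recurrent wheeze at the first wheeze report makes time-to-event incidence too low, and biases the hazard ratio if loss differs by arm

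*Supplement*

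**What the plan says.** Section I.A of the Addendum makes the primary outcome a composite. Its asthma part can be reached at any age: "Asthma will be defined as a parent's report of physician's diagnosis at any time during the first three years of life". Recurrent wheeze needs "at least one report of wheezing in the third year of life plus any report of wheezing in any of the first two years". The added routes, through controller medication or repeated third-year reports, also need third-year data.

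On dating, the Addendum says that "the time of incident recurrent wheezing will be determined by the time of first report of wheezing, for time-to-event analyses". Because the questions were asked every three months and some questionnaires were missed, "event times will be treated as interval-censored". It names no model, gives no rule for children lost before year 3, and does not rank this analysis against the protocol's test. The Summary of Changes to the Analysis Plan lists time-to-event analyses as something brought in, not as a replacement.

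In the Current Protocol, P.2.a tests Aim 1 by logistic regression at age 3 with fixed centre effects. For Aims 1 and 3, VII.K schedules "three interim analyses (conducted at year 3 month 5, year 4 month 5, and year 5 month 5", followed by a final analysis. It adds: "If the boundaries are crossed for efficacy endpoints at any interim analyses, for any of the aims, the study will continue". P.3 describes the interim plan as one to "adjust for the number of times (3) asthma and/or recurrent wheeze will be analyzed over the study period".

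**The concern.** The event date depends on the child's future. Take two children who both first wheeze at 6 months. One stays and reports wheeze in year 3, and becomes an event at 6 months. The other leaves at 20 months. That child's status is unknown, but ordinary right-censoring records 20 event-free months.

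Censoring then removes events as well as follow-up time. This happens even if the reason for leaving has nothing to do with wheeze. The incidence curve is pulled down, and if one arm loses more children, more events vanish from that arm.

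The interim looks use the same outcome, so it also matters how much of it can exist at each look.

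**Working it through.** **1. The plan's own figures.** Inputs from Q.1: 330 per arm, 25% reduction, control incidence 40-50%, two-sided 0.05. The arcsine formula is power = Φ(2|arcsin√p − arcsin√(0.75p)|·√(n/2) − 1.96). At p = 0.50 this is 2 × (0.7854 − 0.6591) × √165 = 3.246, and Φ(1.286) = 0.901. At 50/45/40% it gives 0.901/0.843/0.770, against 0.906/0.837/0.773 in Table 4.

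The spending function α(t) = 4[1 − Φ(z₁₋α/₄/√t)] at t = 0.25, 0.5, 0.75, 1 gives boundaries 4.3326, 2.9631, 2.3590 and 2.0141. The plan states 4.3329, 2.9631, 2.3590 and 2.0141. Both sets of figures reproduce.

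**2. Effect of the dating rule.** This is a large-sample simulation.
- From the documents: control incidence 45% (middle of Q.1's range), treated 33.75%, loss 18%.
- Assumed: 12 quarterly reports; a child-level random effect with SD 0.8 or 2.0; drop-out uniform over the quarters and unrelated to wheeze; censoring at the last report; wheeze-only endpoint; grouped-time proportional hazards model. The unequal loss splits are illustrative.

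| True effect | Loss, control/treated | HR, dated at first wheeze | HR, dated at completing report |
|---|---|---|---|
| None | 18%/18% | 0.995-1.000 | 0.994-0.999 |
| None | 21%/15% | 1.051-1.065 | 0.998-1.009 |
| None | 24%/12% | 1.112-1.114 | 1.000-1.007 |
| None | 12%/24% | 0.893-0.910 | 0.999-1.006 |
| 25% reduction | 18%/18% | 0.682-0.696 | 0.680-0.692 |
| 25% reduction | 24%/12% | 0.765-0.773 | 0.691-0.692 |
| 25% reduction | 12%/24% | 0.620-0.624 | 0.681-0.688 |

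Ranges cover the two random-effect SDs. The complete-case odds ratio at age 3 stayed at 0.99-1.01 in every null scenario.

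With 18% loss, the product-limit 3-year incidence was 40.2-40.7% under first-wheeze dating and 44.9-45.0% under completing-report dating; the truth was 44.9-45.0%. As a check, if no leaver ever counted as an event, the figure would be 0.45 × (1 − 0.18) = 36.9%. The estimate lies between that floor and the truth, as it should. A further run with true incidence 25.3% gave 22.8%.

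**3. Ages at the interim looks.** VII.K puts the looks at study months 29, 41 and 53. VII.L puts first births at month 12 and last births at month 30.
- Oldest child: 29 − 12 = 17, 41 − 12 = 29 and 53 − 12 = 41 months.
- Aged 24 months or more, births assumed uniform: 0; (17 − 12)/18 = 28%; (29 − 12)/18 = 94%.
- Aged 36 months or more: 0; 0; (17 − 12)/18 = 28%.

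VII.L also puts the first 3-year visits at month 53. That implies first births at 53 − 36 = month 17, and oldest ages of 12, 24 and 36 months. On either reading, no child at look 1 has entered the third year. The one-third incidence that Q.1 simulates there, and the 25% information behind the boundary, could come only from asthma diagnoses.

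**4. Cost of the interim looks.** Cumulative alpha is 0.000015, 0.0031, 0.0193 and 0.05. Power at 50/45/40% is 0.896/0.837/0.763 with four looks, against 0.901/0.843/0.770 with one test: 0.5-0.7 points. If only the final look counts, it is 0.892/0.830/0.754, up to 1.6 points lower than one test. With illustrative information of 5%, 28% and 75% at the first three looks, look 1 spends zero to six decimals and the final boundary is 2.011.

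**The case against.** The strongest reply has four parts.

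- P.1 expects loss to be completely at random, and P.2 will check whether it differs by arm. With equal loss the hazard ratio is unbiased. This stands, so a reader who infers that backdating always biases the treatment comparison goes further than the documents allow. Equal random loss does not rescue the incidence curve, though, and P.1 itself allows for fluctuation from differential loss.
- The logistic test in P.2.a uses no event dates. This stands: the main test at age 3 is not threatened. But the Addendum never says which analysis is confirmatory.
- The Addendum does not say how leavers are censored, so censoring at the last report is an assumption. That is fair, but it is the default when no rule is given.
- Dating at onset has a natural meaning, and early asthma diagnoses would dilute the effect. Both stand. Onset is better studied as time to first wheeze, which every child can contribute without a third-year condition.

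**Conclusion.** The point holds for the time-to-event analyses only. Under censoring at the last report, first-wheeze dating understates 3-year incidence by about 4-5 percentage points at 45% true incidence and 18% loss. It shifts the null hazard ratio to about 0.9 or 1.1 for 12% against 24% loss. These sizes rest on a wheeze-only endpoint and the assumptions listed above, and would shrink where asthma is diagnosed early.

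On the interim plan, three stronger readings are tempting and not supported.

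- A reader might infer that every look precedes the endpoint. Recurrent wheeze can be met from 24 months and asthma at any age, and look 3 falls in the month of the first 3-year visits. Only look 1 cannot contain recurrent wheeze.
- A reader might infer that alpha is wasted because a crossing never stops the trial. The cost is about half a power point. VII.K also lets the absence of apparent benefit at interim weigh in a safety stop, and the interim details were added on the DSMB's recommendation.
- A reader might infer that 0.05 in P.3 contradicts the final |z| of 2.0141 (two-sided p = 0.044). It does not: 2.0141 is the final boundary under an overall 0.05. The real slip is P.3's count of three analyses against four in VII.K.

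**What to change.** - In time-to-event analyses, date recurrent wheeze at the report that completes the definition. Start the censoring interval at the last report at which it was not met. Name the model and the censoring rule for children lost before year 3.
- State that the 3-year logistic test is confirmatory.
- Analyse time to first wheeze as a separate outcome; the protocol already defines any wheeze as a phenotype.
- Base interim information for Aim 1 on children with third-year data, and recompute the boundaries by the spending function.
- Correct P.3 to four analyses, with final |z| 2.0141. Removing the interim looks is optional.

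The cost is one changed event-date derivation and some rewording. The downside is that wheeze-only events then fall mostly in year 3, so information on onset moves to the separate analysis.

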## **II. Secondary Analyses.**

**A. Analyses based on levels.** Secondary analyses using baseline and follow-up maternal 25OHD levels will be performed. We will investigate the effect of baseline and follow-up maternal levels separately on the development of primary and secondary outcomes in the trial. Additionally, we will categorize mothers into categories based on joint baseline and follow-up levels. Mothers who have baseline levels and follow-up levels  $\geq 40$  mg/dl will be categorized in the HI-HI group; those who have baseline levels and follow-up levels  $< 40$  mg/dl will be categorized in the LO-LO group; mothers who do not meet these definitions will be categorized either in the HI-LO or LO-HI groups based on their baseline and follow-up levels.

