|------------------------------------------------------------|----------------------------------------------------------------|------------|------------|
|                                                            | 35%                                                     | 30% | 25% |
| 0.50                                                | 0.998                                                          | 0.982      | 0.913      |
| 0.45                                                | 0.992                                                          | 0.958      | 0.858      |
| 0.40                                                | 0.973                                                          | 0.906      | 0.779      |
| 0.35                                                | 0.936                                                          | 0.845      | 0.691      |
| 0.30                                                | 0.890                                                          | 0.736      | 0.608      |
| 0.25                                                | 0.795                                                          | 0.654      | 0.531      |

**O.4. Power for Specific Aim 4.** The research to date on the impact on Vitamin D supplementation of 25(OH)D is presented in Table 1. As noted in the table, only 4 studies have been conducted on pregnant women, all had fewer than 100 subjects, and the maximum daily dose for these studies was 1,600 IU. The only data available on 25(OH)D status in the supplementation ranges we are proposing has been provided by [name] (unpublished data, see section III). In a study of 400 pregnant women (African Americans, Hispanic,

and Caucasians) on either 4000 IU (supplemented) or 400 IU (control) of Vitamin D daily, the maternal plasma 25(OH) D levels were 46 ng/mL in supplemented subjects, and 32 ng/mL in controls after 8 months of supplementation, an overall difference of 14 ng/mL. The estimated standard deviation for 25(OH)D levels in these ranges is 16.

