#### **P.2.b. Plan for Specific Aim 2**

For this analysis, our N will be 800, since most of the dropouts will be expected to occur after delivery. Thus, the expected drop in N due to the 8% miscarriage rate was applied. We will test the hypothesis that the dose of 4,400 IU per day is sufficient to get 90% of the women to a sufficient level of 25(OH)D of at least 75 nmol/L, primarily using a logistic regression model, with randomization group (i.e. intervention group vs. usual care) as the independent variable. The dependent variable will be 25(OH)D level at delivery. We will adjust our analyses for other covariates that may affect 25(OH)D level, such as sun exposure (from the SmartProbe and the sun exposure questionnaire), age, and diet (calculated vitamin D intakes from dietary sources).

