**Table 6. Power to detect a 25-35% reduction in secondary outcomes for 870 subjects in a multi-site study, (effectively 660 patients, assuming an 8% miscarriage rate and 18% loss to follow-up)**

| Mean Incidence of secondary outcome in 400 IU group | Percent reduction in secondary outcome in 4400 IU group |            |            |
|------------------------------------------------------------|----------------------------------------------------------------|------------|------------|
|                                                            | 35%                                                     | 30% | 25% |
| 0.50                                                | 0.998                                                          | 0.982      | 0.913      |
| 0.45                                                | 0.992                                                          | 0.958      | 0.858      |
| 0.40                                                | 0.973                                                          | 0.906      | 0.779      |
| 0.35                                                | 0.936                                                          | 0.845      | 0.691      |
| 0.30                                                | 0.890                                                          | 0.736      | 0.608      |
| 0.25                                                | 0.795                                                          | 0.654      | 0.531      |

**Q.4. Power for Specific Aim 4.** The research to date on the impact of vitamin D supplementation on 25(OH)D is presented in Table 1. As noted in the table, only 4 studies have been conducted on pregnant women, all had fewer than 100 subjects, and the maximum daily dose for these studies was 1,600 IU. The only data available on 25(OH)D status in the supplementation ranges we are proposing has been provided by [name] (unpublished data, see section III). In a study of 347 pregnant women (African Americans, Hispanic,

and Caucasians) on either 4000 IU (supplemented) or 400 IU (control) of Vitamin D daily, the maternal plasma 25(OH) D levels were 115 nmol/L in supplemented subjects, and 80 nmol/L in controls after 8 months of supplementation, an overall difference of 35 nmol/L. The estimated standard deviation for 25(OH)D levels in these ranges is 40.

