# Summary of Protocol Changes

## Summary of Changes to VDAART Protocol

| Table of changes to VDAART Protocol                                                  |                                   |                                                                                                                                     |        |
|--------------------------------------------------------------------------------------|-----------------------------------|-------------------------------------------------------------------------------------------------------------------------------------|--------|
| Change                                                                               | Page/Section                      | Reason for change                                                                                                                   | Date   |
| 1. Change units of 25(OH)D from ng/ml to nmol/L                                      | throughout document               | Recommended change by DSMB                                                                                                          | 8.6.09 |
| 2. Added two paragraphs reviewing vitamin D effects on immune system                 | bottom of page 2 to top of page 3 | Recommended change by DSMB                                                                                                          | 8.6.09 |
| 3. Switched order of Aims 1 and 2                                                    | pages 2-3                         | Steering Committee decision; to conform with scientific aims in NIH grant                                                           | 8.6.09 |
| 4. Changed dose of vitamin D3 for intervention arm from 4,000 IU/day to 4,400 IU/day | throughout document               | Recommended change by DSMB; to account for the 400 IU contained in prenatal vitamins                                                | 8.6.09 |
| 5. Defined current smoker                                                            | page 7                            | Recommended change by DSMB                                                                                                          | 8.6.09 |
| 6. Added to exclusion criteria:                                                      |                                   |                                                                                                                                     | 8.6.09 |

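### Addendum II.A sets the HI/LO cut-point for maternal 25(OH)D at 40 mg/dl, a unit that puts every mother with both levels in LO-LO; the likely intended 40 ng/ml (100 nmol/L) is stated nowhere

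*Supplement*

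**What the plan says.** Addendum, section II.A, opens with a general plan: "Secondary analyses using baseline and follow-up maternal 25OHD levels will be performed". It first provides for baseline and follow-up maternal levels to be related separately to the primary and secondary outcomes, with no cut-point. It then adds a joint grouping. Mothers at or above 40 at both times "mg/dl will be categorized in the HI-HI group"; mothers below 40 at both times "mg/dl will be categorized in the LO-LO group"; the rest are HI-LO or LO-HI.

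The current protocol measures 25(OH)D in nmol/L. Its summary of changes records, for the whole document, "Change units of 25(OH)D from ng/ml to nmol/L". The Aim 2 analysis (P.2.b) uses a "level of 25(OH)D of at least 75 nmol/L". Section Q.4 reports that, in an earlier trial, maternal plasma "25(OH) D levels were 115 nmol/L in supplemented subjects, and 80 nmol/L in controls after 8 months of supplementation", and adds: "The estimated standard deviation for 25(OH)D levels in these ranges is 40". Sections VII.I and VIII use 300 nmol/L as the upper safety limit. The protocol does use mg/dl for serum calcium (VII.I and VII.J), but never for 25(OH)D. The summary of changes to the analysis plan does not mention the unit.

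**The concern.** A classification rule has to be executable as written. This one is expressed in a unit that no 25(OH)D value in the documents comes near, and the unit appears twice, so it is not a single slip within an otherwise clear sentence. A programmer following the text would produce one occupied group and three empty ones.

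The correction also has to be inferred. Keeping the number 40 and changing only the unit leaves two candidates: ng/ml, the unit of the original protocol, or nmol/L, the unit of the current one. They differ by a factor of 2.5 and give very different groups. The four-group comparison depends entirely on where this line falls.

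**Working it through.** **Conversion factor.** The original protocol (O.4) gives the same planning means in the older unit: "25(OH) D levels were 46 ng/mL in supplemented subjects, and 32 ng/mL in controls". The current protocol gives 115 and 80 nmol/L.
- 115 / 46 = 2.5 and 80 / 32 = 2.5.
- The Aim 2 threshold agrees: 75 / 30 = 2.5.

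**Check that the protocol's SD and unit are coherent.** The Addendum derives no figure of its own, so Table 7 of the current protocol serves as the check. Inputs: 330 per arm, SD 40 nmol/L, two-sided alpha 0.01.
- Standard error = 40 × √(2/330) = 3.114.
- Difference 12.5: 12.5 / 3.114 = 4.014; Φ(4.014 − 2.576) = 0.925. Table 7 states 0.925.
- Difference 7.5: 7.5 / 3.114 = 2.408; Φ(2.408 − 2.576) = 0.434. Table 7 states 0.444, from simulation.

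The original protocol's SD of 16 ng/ml with differences of 5 and 3 gives the same values. The SD and the factor 2.5 hold.

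**The cut-point as written.**
- 40 mg/dl = 40,000,000 ng per 100 ml = 400,000 ng/ml.
- 400,000 × 2.5 = 1,000,000 nmol/L.
- Against the safety limit: 1,000,000 / 300 ≈ 3,300.
- Against the expected supplemented mean: 1,000,000 / 115 ≈ 8,700.

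The HI share is therefore 0% at both times, and every mother with both measurements is LO-LO.

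**The two candidate corrections, at follow-up.** Share HI = Φ((mean − cut) / 40), normality assumed. The overall column averages two equal arms.

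| Cut-point | Control (mean 80) | Supplemented (mean 115) | Overall |
|---|---|---|---|
| 40 ng/ml = 100 nmol/L | Φ(−0.5) = 31% | Φ(0.375) = 65% | 48% |
| 40 nmol/L = 16 ng/ml | Φ(1) = 84% | Φ(1.875) = 97% | 91% |

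A lognormal with the same means and SD gives 24%, 60% and 42% at 100 nmol/L, and 89%, over 99% and 94% at 40 nmol/L. The gap does not depend on the shape.

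**Joint groups.** These need a baseline distribution, which the documents do not give for this trial. As an assumption, take a bivariate normal with baseline mean 40 to 75 nmol/L, baseline SD 25 to 40 and correlation 0.3 to 0.6, with the follow-up figures above. The ranges across those settings are:

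| Cut-point | HI-HI | LO-LO |
|---|---|---|
| 100 nmol/L | about 1–20% | about 42–52% |
| 40 nmol/L | about 47–85% | about 2–8% |

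**The case against.** The strongest reply is that this is a labelling slip whose meaning is plain. Section I of the current protocol describes 25 to 62.5 nmol/L as insufficient (in a sentence about infants), and the maternal target is 75 nmol/L. Calling a mother at 40 nmol/L HI would contradict both. By contrast, 100 nmol/L lies above the target and between the two expected means, and ng/ml was the trial's earlier unit. This stands: the two readings are not equally plausible. It does not remove the defect, because the Addendum neither says ng/ml nor gives a value in the protocol's current unit.

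Several stronger readings are tempting and are not supported.
- A reader might infer that the Addendum's whole level-based analysis fails. It does not: the separate analyses of baseline and follow-up levels come first and use no cut-point.
- A reader might infer that confounding was ignored. Section II.A names no covariates, but Table 3 of the protocol lists potential confounders of this very relationship, between 25(OH)D and asthma or recurrent wheeze. What is lacking is a cross-reference.
- A reader might treat the departure from 75 nmol/L as an error. A secondary grouping may use a different threshold from Aim 2.
- A reader might suspect that the cut-point was left open so that it could follow the results. Nothing in the documents shows this; the number 40 is fixed and only its unit is wrong.

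The planning means are also imperfect for this purpose. They come from another trial after 8 months of supplementation, whereas here enrolment is at 10–18 weeks and follow-up blood at 32–38 weeks, an interval of 14 to 28 weeks. The shares above are illustrative.

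**Conclusion.** The cut-point is wrong as written. Taken literally, it leaves one occupied group out of four among mothers with both levels measured, and the joint analysis cannot be run. This part is pure unit conversion and rests on no assumption.

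The likelier intended value is 40 ng/ml (100 nmol/L), but that is an inference. The size of the choice, 65% and 31% HI at follow-up against 97% and 84%, rests on the protocol's borrowed means and SD and on normality. The joint group sizes rest in addition on an assumed baseline distribution.

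The effect is confined to one secondary, non-randomised grouping. The primary intention-to-treat comparison and the separate-level analyses do not use the cut-point.

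**What to change.** Replace mg/dl in both places in Addendum II.A and state the cut-point in nmol/L, the current protocol's unit, for both baseline and follow-up: 100 nmol/L if 40 ng/ml was meant. Record the correction in the summary of changes to the analysis plan. The cost is one corrected sentence and one log entry, with no new data.

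Optionally, cite the Table 3 confounders for this analysis and label it observational, because the groups are formed partly on a level measured after randomisation.
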